## Discussion

To date, no randomized studies have been conducted to evaluate the benefits and challenges associated with longer ART dispensing intervals in resource-limited settings. This study will be the first to compare standard of care, 3-month, and 6-month ART dispensing intervals for stable, HIV-infected individuals in Malawi and Zambia. We focus on outcomes that are relevant to national HIV programs and that could result in widespread policy changes. Results from the study will help limited-resource health systems better understand the full scope of outcomes resulting from various ART dispensing intervals and help to inform health policy decisions. Our study is innovative in that it includes qualitative data collection from patients and providers. These data can help to address questions about moving to longer dispensing intervals, including around patient experiences transporting a large supply of medications (6 months of ART, CPT, and/or IPT), patient challenges with storage of these large supplies, particularly for those who have not disclosed to other members living in the same household, and concerns that patients given a large supply of ART may be inclined to sell medications for income or provide them to friends or family. We will also estimate both total costs of implementation and cost-effectiveness. Cost savings are widely anticipated from adopting longer follow-up intervals, but such savings have yet to be demonstrated or quantified in real-world settings, making the economic evaluation essential for resource allocation decisions.

This study has several limitations. Apart from the entry viral load, the study will not perform follow-up viral load testing. Therefore, results for the secondary outcome of viral load will be limited to those tests performed within the context of routine care. In Zambia, viral load monitoring is performed annually, and in Malawi, monitoring occurs every 2 years. We anticipate that viral load results may be missing from a large number of participants as these programs are both early in their viral load scale-up efforts. Because of these concerns, viral suppression is a secondary outcome. Our definition of a “stable” ART patient was developed in conjunction with HIV experts and takes into consideration published literature on this topic [2, 15–17]. Our results may not be generalizable in settings that use a different definition of stable. There may be a subset of unstable ART patients who struggle with retention because of circumstances that prevent frequent follow-up to an ART facility (living remotely, difficult work schedule, school or work outside of the country). These individuals could benefit from a 6-month dispensing interval, but they will not be included in our study, and their outcomes will not be captured.

Participant blinding will not be used in the trial as there is no way to blind providers or patients to their assigned group. Lack of blinding could potentially influence the study results as participants who are motivated to have a longer drug supply could transfer to a study facility with 6-month dispensing. Additionally, regardless of arm, participants may be more likely to be retained if they know they are being followed as part of a study. We have attempted to reduce bias by limiting interaction with study participants to the screening and entry visits, which will both coincide with routine ART visits. All subsequent data will be obtained from medical record review with the exception of a small subset of participants (n = 240 across both countries) who will be asked to complete in-depth interviews at the end of the first year. These limitations will be noted in study findings when they are presented.

It is possible that Malawi and Zambia will revise their HIV treatment guidelines during study follow up, including extending dispensing intervals to 4 months or longer. In Malawi, IPT rollout in high-burden TB districts is anticipated during the first year of the study, and this will result in patients returning to clinic for extra visits to adhere to the IPT monitoring schedule (monthly for the first 3 months of treatment). These national guideline changes will be captured at the level of individual participant data and accounted for in our analyses, but they may influence our ability to measure intended study outcomes. Finally, the study will be working alongside Ministry of Health in both Malawi and Zambia to ensure that sites randomized to 6 months will have adequate supplies of ART, CPT, and IPT. Should countries adopt 6-month dispensing, this high level of support would be unlikely to be available at all sites, resulting in potential challenges with procurement, supply chain, and/or storage.

Despite these limitations, this study will be the first randomized effort to measure multi-month ART dispensing intervals on the outcomes of retention, virologic suppression, and cost-effectiveness. If 6-month dispensing intervals are proven to be non-inferior and cost-effective, the results may help to inform ART dispensing standard of care guidelines in Malawi, Zambia, and other limited-resource health systems.

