### Intervention

This study will compare standard of care to two alternative dispensing strategies. Under standard of care, ART dispensing intervals are based on provider opinion. Malawi and Zambia ART guidelines recommend 3-month dispensing for stable patients, but adherence to guidelines is variable and dispensing may vary due to provider and/or patient preference or medication availability. Participants in the 3-month dispensing study arm will receive a 90-day supply of ART and will have routine clinic visits every 90 days. Participants in the 6-month dispensing study arm will receive a 180-day supply of ART and will have routine clinic visits every 180 days. For all arms, other HIV services will be standard of care and supplies of co-trimoxazole (CPT) and isoniazid (IPT) will also be provided based on the assigned ART dispensing interval and country-specific guidelines about use of these therapies as part of routine HIV care.

Pharmacy support will be provided as part of the study, to ensure medication stock outs do not occur at study sites and that study sites do not take drug stocks away from non-study facilities. The trial is being conducted in close collaboration with the Ministries of Health in Malawi and Zambia and USAID, with support from the Supply Chain Management Systems (SCMS). Participants in the 6-month arm will be offered generic plastic bags to assist with carrying the large supply of medications. Participants will be given information about “ideal” basic storage conditions for medications, particularly in regard to temperature and avoidance of storage in direct sunlight. Participants who provide written informed consent will be willing to participate in any of the study arms; however, those in the 6-month arm may request a reduction in refill duration at any point during follow up. The proportion of individuals changing from 6-month ART dispensing to shorter intervals and reasons for changing will be captured during follow up.

To measure the primary outcome of retention, data will be abstracted from participants’ medical records. In Malawi and Zambia, default from care is defined as being out of ART for more than 60 days, and this definition will be used for the endpoint of retention (<60 days without ART at each time point).

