### Blinding and allocation

Random assignment of matched clusters will be determined by computer. Clusters will be matched based on available information that could potentially predict outcomes, including ART cohort size and region. Matched clusters will then be randomly allocated with one receiving the 3-month intervention, one the 6-month intervention, and one the control condition. Allocation will be completed by the study analyst. Clusters will then be informed of the allocation. No attempt will be made to blind the sites or patients to their allocated group, as both providers and patients will be aware of the amount of medication dispensed and the timing between appointments.

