### Study population and sample size

HIV-infected individuals age 18 years or older who are considered stable on ART will be enrolled in the study. The definition of “stable on ART” and other inclusion and exclusion criteria are summarized in Table 1. Since there is no universally accepted definition of stability, criteria were developed for the study based on the expert opinion of infectious diseases specialists. As this is a cluster-randomized trial, study participants will receive the dispensing strategy that was randomly assigned to the cluster (health facility) at which they receive their HIV care.

**Table 1 Tab1:** Study inclusion and exclusion criteria

Inclusion criteria
• Confirmed HIV-1 infection based on country standard of care for testing algorithm
• Stable on ART, defined as:
− on ART for at least 6 months
− on a first-line ART regimen as defined by country-specific guidelines (efavirenz, tenofovir, and emtricitabine or lamivudine)
− no drug toxicity/tolerability issues within the prior 6 months
− no period of more than 1 month without medication possession within the last 6 months
− no active opportunistic infection (OI) suspected (including tuberculosis (TB)) and not treated for an OI within the last 30 days
− undetectable viral load (as defined by country guidelines) within the last 6 months:
▪ Malawi: less than 1000 copies/mL
▪ Zambia: less than 20 copies/mL
• Willing and able to provide written informed consent
• Planning to receive HIV care from the same facility for at least 1 year
Exclusion criteria
• Co-morbid condition(s) for which the individual is treated at the ART clinic (hypertension, diabetes mellitus, chronic lung disease, etc.)
• Pregnant or breastfeeding, or if not breastfeeding, less than 6 months postpartum
• Already receiving care within a differentiated model in which care is received as a group or in a community, such as a community-based adherence group or adherence club
• Enrolled in any other research studies that would influence ART adherence, retention, or dispensing interval

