### Sample size

Our study sample size was estimated for a cluster-randomized non-inferiority trial. With 30 clusters available for randomization, we estimated the sample size assuming a fixed number of clusters (*k*), an equal number of clusters per arm, and an equal number of subjects per cluster. Using a one-sided *Z* test (unpooled) with a significance level of 0.05, we estimated that about 5% of subjects would fail to be retained in care in the standard of care arm and 7.5% to be non-inferior in the 3-month or 6-month study arms. Assuming power of 90% and an intracluster correlation coefficient (ICC) of 0.004 [11], we will need to enroll 271 subjects per cluster for a total of 2710 subjects per arm and 8130 total individuals.

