#### Entry visit data collection

All patient baseline data will be collected in the entry visit, which may come immediately after screening for eligible patients, or may take place at the next visit when a viral load result is available. Two types of data will be collected at the entry visit. First, the participant’s medical record will be reviewed to collect clinical history, including date of HIV diagnosis, date of ART initiation, use of CPT and/or IPT, and history of ART clinic visits and ART dispensing intervals in the prior 12 months. The second type of data will come from an interview with the patient. In the interview, the study interviewer will obtain sociodemographic information about the participant, including gender, highest level of education, household composition, employment status, HIV disclosure status, and travel and opportunity costs related to the participant’s ART clinic visits. After completion of the entry visit data collection, the participant will complete her or his routine clinic visit with site providers and receive ART dispensing as per the site randomization. If CPT and/or IPT dispensing is standard of care for the facility, CPT and/or IPT will also be provided as per the randomized dispensing interval.

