#### Follow-up data collection

Retention and virologic suppression will be assessed 12, 24, and 36 months after the entry visit date. At each of these time points, data from participants’ medical records will be collected by study staff. Data will include number, timing, and reason for clinic visits, retention in care (and if not retained, reason), possession of ART based on number of pills dispensed at each visit, possession of CPT and/or IPT based on number of pills dispensed at each visit, and viral load. Study staff will allow up to 60 days after a time point has been reached before medical record review, allowing for participants to meet the protocol-defined definition of default. For participants who default, facility standard of care procedures for tracing may be used, but the study will not make contact with the participant for the purposes of facilitating return to care.

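### Enrolment follows open allocation, and no entry rule bars patients who arrive because a facility offers 6-month dispensing; this could bias the comparison, plausibly in favour of that arm.

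*Protocol article*

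**What the plan says.** The order of events has to be pieced together from several sections of the protocol article. Under Blinding and allocation, matched clusters are randomised by computer, and "Clusters will then be informed of the allocation". The same section says that neither sites nor patients are blinded. Under Eligibility screening, study staff recruit patients in ART clinic waiting areas. Under Entry visit data collection, a participant is dispensed ART at the entry visit according to the site's arm. Individual enrolment therefore comes after the arm is known at the facility.

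The Discussion names the consequence: "participants who are motivated to have a longer drug supply could transfer to a study facility with 6-month dispensing". The countermeasure that follows is to limit staff contact with participants, and the limitations are to be noted when findings are presented.

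Table 1 has one criterion that concerns the facility: "Planning to receive HIV care from the same facility for at least 1 year". It also asks for at least 6 months on ART, without tying that time to the enrolling facility. Past attendance is recorded at entry, as "history of ART clinic visits and ART dispensing intervals in the prior 12 months", but it is not an eligibility rule.

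**The concern.** When individuals are recruited after their cluster's arm is known, randomising the clusters no longer ensures comparable participants. Those who enter the 6-month arm may differ from those who enter the other arms because of the allocation itself. The article describes movement in one direction only, towards the 6-month sites, and limiting staff contact neither prevents nor detects it.

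The margin is narrow. The sample size assumes that "5% of subjects would fail to be retained in care in the standard of care arm and 7.5% to be non-inferior", a gap of 2.5 percentage points. If patients who go out of their way to reach a 6-month site are better retained than the site's usual patients, they dilute its failure rate and make a false finding of non-inferiority more likely. That is the conclusion the trial hopes to reach and offers to national programmes.

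The article handles a comparable threat differently. Under Qualitative data collection, interviewed participants, less than 3% of the sample, are excluded from outcome analyses after the first year because the interview might affect retention. Movement driven by allocation gets no analytic safeguard.

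**Working it through.** **Inputs from the Sample size section.** One-sided unpooled Z test "with a significance level of 0.05"; 90% power; failure 5% under standard of care, non-inferiority limit 7.5% (margin 0.025); ICC 0.004; 10 clusters per arm; 271 per cluster, 2710 per arm, 8130 in total.

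**Reproducing the plan's figure.** With true failure of 5% in both arms:

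- Before clustering: n = 2 × 0.05 × 0.95 × (1.645 + 1.282)² / 0.025² = 1301.7 per arm.
- With k = 10 fixed clusters: m = n(1 − ICC)/(k − n × ICC) = 1301.7 × 0.996/(10 − 5.207) = 270.5, rounded up to 271.
- Totals: 2710 per arm and 8130 overall. Both match.

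**Model for the check.** Design effect = 1 + 270 × 0.004 = 2.08. Effective n = 2710/2.08 = 1303 per arm. For comparator failure p0 and 6-month failure p6:

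- SE = √{[p0(1 − p0) + p6(1 − p6)]/1303}
- P(declare non-inferiority) = Φ[(0.025 − (p6 − p0))/SE − 1.645]

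At p0 = p6 = 0.05 this gives 90.0%, the planned power. At p0 = 0.05 and p6 = 0.075, SE = 0.00947 and the result is 5.0%, the planned error rate.

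**Effect of arrivals.** Suppose a fraction f of the 6-month arm are arrivals with failure q, and the rest have true failure at the limit. The arm's observed rate is then p6 = (1 − f) × 0.075 + f × q. The documents give neither f nor q, so both are assumptions.

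| f | q | p6 | difference from 5% (points) | false non-inferiority |
|---|---|---|---|---|
| 5% | 2% | 7.225% | 2.225 | 8.8% |
| 5% | 5% | 7.375% | 2.375 | 6.5% |
| 5% | 10% | 7.625% | 2.625 | 3.8% |
| 10% | 2% | 6.95% | 1.95 | 14.6% |
| 10% | 5% | 7.25% | 2.25 | 8.4% |
| 10% | 10% | 7.75% | 2.75 | 2.8% |

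Worked row (f = 10%, q = 2%): p6 = 0.9 × 0.075 + 0.1 × 0.02 = 0.0695; SE = 0.00928; (0.025 − 0.0195)/0.00928 − 1.645 = −1.052; Φ = 14.6%.

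In head counts, f of 5% or 10% means about 14 or 27 of the 271 participants at each 6-month site.

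The sign depends on q. Arrivals who fail at less than 7.5% raise the false non-inferiority rate, and arrivals who fail at more than 7.5% lower it.

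**The case against.** Four points can fairly be made against this.

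- **The risk is disclosed, and the quoted sentence is about participants.** Extending it to patients who arrive and then enrol is an inference. It is a short one, because the motive is the same and Table 1 would admit such a patient. Disclosure does not protect the error rate.
- **Entry is not easy for a newcomer.** An arrival needs 6 months on ART, no gap of more than 1 month in medication possession, and a qualifying viral load within 6 months. Those without a viral load result wait until their next routine visit and are screened again. Enrolment was planned to run only from 31 May to 30 November 2017. These conditions make large numbers less likely, but they do not bar recent arrivals.
- **Size and direction are assumed.** This stands. Patients who want fewer visits may be the ones who find attendance hardest, and the table shows that the effect then reverses.
- **A restricted analysis is ordinary SAP content.** That is true of the analysis version. The eligibility criteria, however, are set out in this article, and so is its stated response to transfer.

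A reader might go further and infer that participants who leave a standard-of-care or 3-month site for a 6-month site are counted as failures, which would tilt the result a second time. The article does not support that. It defines default by time off treatment rather than by leaving a facility, and says that "this definition will be used for the endpoint of retention (<60 days without ART at each time point"). Someone who moves and keeps receiving ART meets that definition. Staff also abstract "retention in care (and if not retained, reason"). How a documented transfer is scored is not stated and may be in the full protocol or SAP.

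**Conclusion.** The point holds as a missing safeguard against selection that depends on allocation. Enrolment follows open allocation, the article concedes movement towards 6-month facilities, and Table 1 does not require attendance before the allocation was known. The first of these is inferred from three sections, since no single sentence gives the order.

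The comparison could be biased, plausibly towards 6-month dispensing. The documents do not show that it is. The range of 6.5–14.6% against a nominal 5% rests on four assumptions: arrivals are 5–10% of the 6-month arm, their failure is 2–5%, true failure among the rest is at the 7.5% limit, and the ICC is 0.004 as planned. With 10% failure among arrivals, the rate is 3.8% or 2.8%. No figure is given here for departures, because their scoring is not stated.

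**What to change.** Add an inclusion criterion: at least one recorded ART visit at the enrolling facility before the date on which that facility's allocation was disclosed. If enrolment cannot be amended, prespecify a sensitivity analysis of the primary outcome restricted to participants who meet this condition. Use the 12-month visit history abstracted at entry, where it identifies the facility of each visit. The article does not say that it always does, so this should be checked first. In either case, report the number excluded by arm. An excess in the 6-month arm would itself show whether such movement took place.

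The cost is a short amendment, or a few lines of analysis-plan wording and one extra analysis. The downside is a small loss of recently arrived patients. The restriction tests for the bias among patients with a usable visit history; it cannot rule out every form of selection after open allocation.

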## Trial status

This manuscript was developed using study protocol version 2.4, 22 June 2017, for “The INTERVAL Study: Varying Intervals of ART Dispensing to Improve Outcomes in HIV”. Recruitment and enrollment began 31 May 2017. Enrollment is expected to be completed by 30 November 2017.

## Abbreviations

aOR: Adjusted odds ratio
ART: Antiretroviral therapy
CI: Confidence interval
CPT: Co-trimoxazole prophylaxis therapy
HIV: Human immunodeficiency virus
ICC: Intracluster correlation coefficient
IPT: Isoniazid preventive therapy
IQR: Interquartile range
OI: Opportunistic infection
PEPFAR: U.S. President’s Plan for Emergency AIDS Relief
TB: Tuberculosis
USAID: United States Agency for International Development
